#### Proceeding With TKA

Following exposure to the education program (intervention arm) or standard care (control arm), all participants will be asked if they will be proceeding with their TKA and, if so, to confirm the date of the procedure.

#### Expectation Fulfillment

The level of expectation fulfillment or satisfaction to undertake goals identified will be determined at 6 months after TKA for participants who proceeded with surgery.

For the HSS-TKR items, participants will be asked to indicate the extent of fulfillment of the expectations, identified prior to surgery, using a 5-point Likert scale, ranging from 5 (completely) to 1 (not at all).

The DQO Index will be repeated post TKA, and differences with values obtained prior to TKA will be indicative of the ability to achieve the task.

For activity expectations identified in the pre-TKA assessment, participants will be asked to rate how satisfied they were that each activity could be undertaken using a 7-point Likert scale ranging from 1 (completely dissatisfied) to 7 (completely satisfied).

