#### Health Literacy

Health literacy is defined as the degree to which individuals can obtain, process, understand, and communicate about health-related information needed to make informed health decisions [72]. In this study, we will assess participants’ health literacy using the shortened version of the HLS-EU-Q12 [53]. Participants will be presented with a number of competencies encompassing information relating to health care, disease prevention, and health promotion and covering 4 cognitive domains, including proficiency in accessing, understanding, appraising, and applying health information. Respondents will rate the level of difficulty in undertaking each competency on a 4-point scale ranging from 1 (very difficult) to 4 (very easy), with higher total scores indicative of higher health literacy. In this study, participants will be asked to complete the HLS-EU-Q12 at study entry (prior to their TKA) and at 6 months after their surgery.

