#### Satisfaction

At 6 months after the TKA, all participants who underwent surgery will be asked to respond to the following:

*Overall, how would you describe the results of your operation?*

Participants will provide a response on a 5-point Likert scale, ranging from 1 (poor) to 5 (excellent).

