#### Feedback Survey

A study participation evaluation survey will be included at the end of the study to enable participants to provide the research team with feedback regarding the intervention and assessments they were asked to undertake and the overall conduct of the study. It will also give study participants the opportunity to provide ideas for future areas of research they consider important to be addressed in recovery from TKA surgery. For those who did not proceed with undergoing a TKA, information will be collected regarding alternate treatment procedures they have undertaken.

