### Secondary Outcomes

The following secondary outcomes will also be evaluated:

The number of participants who decide not to proceed with their TKA.The level of patient expectation fulfillment derived from the HSS-TKR questionnaire, the DQO Index, and activity expectations, conducted 6 months after the TKAThe level of patient satisfaction with surgical outcomes assessed at 6 months after the TKA.A change in patient health literacy (within individual patients’ scores), derived from the HLS-EU-Q12, conducted at study entry and at 6 months after the TKA

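### Follow-up health literacy is timed only from surgery, so participants who decide against surgery have no second measurement and the comparison is not of all randomised participants

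*Protocol article*

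**What the plan says.** All references are to the protocol article.

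- **Purpose.** Study Stages says that the randomised stage will assess the intervention's impact on fulfilment, satisfaction and health literacy.
- **Health literacy.** The Health Literacy section states that "participants will be asked to complete the HLS-EU-Q12 at study entry (prior to their TKA) and at 6 months after their surgery". Secondary Outcomes defines the outcome as within-patient change, "conducted at study entry and at 6 months after the TKA". The only post-surgical column in Table 1 is also counted from the operation.
- **Not proceeding.** After the programme or standard care, "all participants will be asked if they will be proceeding with their TKA" (Proceeding With TKA). The first item under Secondary Outcomes is "The number of participants who decide not to proceed with their TKA".
- **Fulfilment and satisfaction.** Fulfilment "will be determined at 6 months after TKA for participants who proceeded with surgery". For satisfaction: "At 6 months after the TKA, all participants who underwent surgery will be asked to respond to the following".
- **Non-proceeders.** The one item of late data specified for them is in the Feedback Survey section: "For those who did not proceed with undergoing a TKA, information will be collected regarding alternate treatment procedures they have undertaken".
- **Length of involvement.** Stage 2, under Study Design, gives 32 weeks from study entry, with at most 6 weeks between a patient's consent to surgery and the operation.

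**The concern.** The decision to proceed comes after randomisation and after exposure to the videos, and the trial counts it as an outcome. The design therefore allows that the two arms may differ in who goes on to surgery. If an outcome is then recorded only in those who had surgery, the arms being compared are no longer the randomised ones. They could differ on that outcome even if the programme did nothing to it.

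For fulfilment of expectations and satisfaction with an operation there is no way round this, because neither is defined for someone who had no operation. Health literacy is different. It exists for every participant, is measured in every participant at entry, and is a stated target of the programme. It loses its follow-up value in non-proceeders only because the form is dated from surgery. Selection related to literacy is plausible: the Background links low health literacy to lower expectations of surgery, and expectations are what the videos aim to change.

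The matter belongs to data collection. No analysis plan can recover a questionnaire that was never sent.

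**Working it through.** **1. The plan's own figure.** The article gives no rate of not proceeding and no calculation for health literacy. Its one computed figure is the primary-outcome sample size (Power Calculation): 6 points, SD 12, α = 0.05, power 80%, 64 per group. The normal approximation with two-sided α gives 2 × (1.960 + 0.842)² × 12² / 6² = 62.8, so 63. The two-sample t test gives 63.8, so 64. The figure reproduces and is not in question.

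**2. Who has a follow-up value, as written.**

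| Outcome | Timing | Defined without surgery? | Value for a non-proceeder |
|---|---|---|---|
| Primary (change in HSS-TKR score) | 3 weeks before scheduled TKA | Yes | Yes |
| Number not proceeding | Asked after the intervention | Yes | Yes |
| Fulfilment | 6 months after TKA, operated only (explicit) | No | None possible |
| Satisfaction | 6 months after TKA, operated only (explicit) | No | None possible |
| Health literacy change | Entry and 6 months after TKA | Yes | None scheduled |

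Only the last row combines an outcome that exists for everyone with a schedule that leaves some participants out. In that row the exclusion follows from the timing; the text does not state it as a restriction.

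**3. Size under assumptions.** Assume that the programme has no effect on health literacy, no control participant declines, a fraction q of the intervention arm declines, and decliners would have scored k SD lower than the arm's average on the outcome. The mean of those remaining is then raised by

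shift = q × k / (1 − q), in SD units.

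| q (number of 75) | k = 0.5 | k = 1.0 |
|---|---|---|
| 2% (1.5) | 0.02 × 0.5 / 0.98 = 0.010 | 0.020 |
| 5% (3.75) | 0.05 × 0.5 / 0.95 = 0.026 | 0.053 |
| 10% (7.5) | 0.10 × 0.5 / 0.90 = 0.056 | 0.111 |

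For scale, the standard error of a difference with 64 per arm is √(2/64) = 0.18 SD. Every value in the table is below that.

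**4. Worst case.** Suppose instead that the extra decliners are exactly the most extreme participants on the outcome. With a normal outcome and trimmed fraction q = (p_control − p_intervention) / p_control, the bound is φ(z₁₋q) / (1 − q). Assumed proceeding rates of 98% v 95%, 97% v 90% and 98% v 85% give q = 0.031, 0.072 and 0.133, and bounds of 0.07, 0.15 and 0.25 SD. These are limits on invented rates and should not be read as expected values.

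**5. Is a matching time point available?** The longest wait of 6 weeks plus 6 months (about 26 weeks) is 32 weeks, the length of involvement that the article already states. A form sent at 32 weeks from entry would therefore fall at about the same point for a non-proceeder as the 6-month form does for an operated participant.

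**The case against.** The strongest reply is that the article never excludes non-proceeders from the health literacy form. The limit to operated patients is written only for fulfilment and satisfaction, the Health Literacy section speaks simply of participants, and how a form is triggered after a cancelled operation is a detail that an article may leave to the full protocol. Patients are also referred only once they have agreed to surgery, with a short wait, so few may decline. A few absent forms would then be ordinary missing data in a trial that already allows for about 15% dropout.

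Part of this stands. The exclusion is inferred from timing, and the effect is small if few decline. But the article does fix the time point, in two sections and Table 1, and gives no alternative for a participant who has no operation. The dropout allowance protects numbers; it does not protect the comparability of the arms when the loss follows a decision that the programme may influence.

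A reader might go further and infer three things that the document does not support:

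- **That all 6-month comparisons are faulty.** For fulfilment and satisfaction the restriction is unavoidable and stated, and the number not proceeding is already reported as an outcome. Further sensitivity analysis there is a matter for the analysis plan, which is not shown.
- **That the plan names declining surgery as an effect of the programme.** It lists it as an outcome and predicts nothing.
- **That the bias should be judged against 0.5 SD.** That ratio (6/12) belongs to the primary outcome, which is measured before surgery.

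**Conclusion.** The point holds for health literacy and is modest. As written, a participant who decides against surgery has no follow-up health literacy score, so an outcome intended to show the programme's impact would be compared in a group defined after randomisation, although it could be measured in everyone.

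The size cannot be fixed from the document, because no rate of not proceeding is given. If 2% to 10% of one arm decline, none in the other, and decliners sit 0.5 to 1 SD lower, the spurious difference is about 0.01 to 0.11 SD. Larger values need both a wide gap in proceeding rates and extreme selection. With very few decliners the effect is negligible. The primary outcome is not affected.

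One matter is left open: the Replacements section replaces participants who withdraw before surgery, within the same arm, but does not say whether declining surgery counts as withdrawal. If it does, replacement could add to the selection.

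This is worth correcting because it costs little and cannot be repaired after data collection.

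**What to change.** - **Health Literacy, Secondary Outcomes and Table 1:** add that participants who do not proceed complete the HLS-EU-Q12 at 32 weeks from study entry, alongside the end-of-study survey already planned for them. The time point for operated participants stays as it is.
- **Data Analysis, Stage 2:** state that change in health literacy is compared between the arms in all randomised participants.
- **Fulfilment and satisfaction:** present any comparison between arms as conditional on having had surgery, next to the proportion proceeding in each arm.

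The cost is one further 12-item form for what is likely to be a handful of participants, and two or three sentences of text. Sample size, the primary outcome and the visit schedule for operated participants do not change.

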### Aims and Objectives

In the current project, we will collaboratively develop a novel educational program for patients undergoing TKA with orthopedic care teams, consumer advocates, and key health care provider stakeholders, which will focus on providing information that will inform and encourage patients to set realistic expectations of TKA surgical outcomes. The ability of the program to influence the type of expectations patients set prior to surgery will be assessed by comparing patients’ expectations before and after the program and by comparing expectations of those who participate in the program to those who receive “standard clinical care” alone. In addition, the project will determine if education program participation is associated with a higher level of expectation fulfillment, satisfaction with surgical outcomes, and improvement in health literacy. We will apply a number of different methods to define patients’ expectations, using both closed- and open-ended questionnaires to evaluate the scope of responses achieved by each approach.

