#### Direct Questioning of Objectives Questionnaire

Methods comparable to those applied by Karunaratne et al [70], using open-ended questions related to participant expectations, will be applied. Participants will be asked to list at least 1 and up to 5 of their most important expectations of TKA surgical outcomes, and then an assessment will be given for two domains for each expectation on 11-point numerical rating scales: (1) the importance of each expectation and (2) the current ability to achieve the task / item. The reported values for importance and ability will be interpreted as “low” if ≤5, and “high” if ≥8. A Direct Questioning of Objectives Questionnaire Index (DQO Index) will be derived from the product of the score for each domain.

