To determine the impact of the health education program to change expectations, the primary outcome measure (HSS-TKR) will be measured and compared between the 2 treatment arms. The within-patient changes of the open-ended measures of patient expectations between T_0_ and T2 will also be compared between the 2 treatment arms to further inform the efficacy of the education platform intervention. We will use data from all participants post surgery to determine the association between expectation fulfillment and overall satisfaction. Activity expectation fulfillment satisfaction and overall procedure satisfaction generate ordinal datasets with associations between the 2 measures undertaken using Spearman rank correlation coefficients.

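### The DQO Index is importance times ability, so its change after TKA does not indicate ability alone, and equal recovery could score differently by arm

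*Protocol article*

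**What the plan says.** In the section on the Direct Questioning of Objectives Questionnaire, participants name one to five expectations and rate each on two 11-point scales: "1) the importance of each expectation and (2) the current ability to achieve the task / item". The Index "will be derived from the product of the score for each domain". That section also sets low and high bands for each rating (5 or below, 8 or above).

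Under Expectation Fulfillment, the Index is repeated after surgery and "differences with values obtained prior to TKA will be indicative of the ability to achieve the task". Under Secondary Outcomes, it is one of three measures of a listed outcome: "The level of patient expectation fulfillment derived from the HSS-TKR questionnaire, the DQO Index, and activity expectations".

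Table 1 collects the DQO at baseline and after the intervention, under Expectations, and again at 6 months under fulfilment. The Stage 2 data analysis says that within-patient changes in the open-ended expectation measures before surgery "will also be compared between the 2 treatment arms to further inform the efficacy of the education platform intervention". The purpose of the programme is given under Aims and Objectives: "The ability of the program to influence the type of expectations patients set prior to surgery will be assessed".

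**The concern.** The definition and the interpretation do not match. A product moves when either factor moves, so a difference in the Index cannot be read as a difference in ability unless importance is held still. Nothing in the article holds it still.

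In most trials this would only add noise. Here the randomised treatment is education intended to alter expectations, and both the HSS-TKR and the DQO capture expectations at least partly as importance ratings. The Background also describes earlier education as lowering expectation levels. The nuisance factor in the fulfilment score is therefore a plausible direct target of the treatment. Two arms with the same functional recovery could show different DQO fulfilment, and the difference could be misread as an effect of the programme on outcome.

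The same mixture affects the comparison before surgery. There the Index is listed as an expectation measure, although one of its two factors is what the patient can do now.

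**Working it through.** The article gives no numerical figure for the DQO Index, so there is none to reproduce. The check is algebraic, followed by an illustration.

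**Inputs from the article.** Index = I × A, where I is importance and A is current ability. There are two pre-TKA values (baseline and post-intervention) and one at 6 months.

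**Assumed inputs.** Each 11-point scale runs from 0 to 10. All ratings below are invented for illustration and refer to a single item.

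**Change within a patient.**

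I6·A6 − Ipre·Apre = Ipre·(A6 − Apre) + A6·(I6 − Ipre)

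The second term vanishes only if importance does not change. The first term is still scaled by importance, so it is comparable between arms only if importance is equal between them. A simple case: 10 × 3 = 30 before and 5 × 6 = 30 after. Ability has doubled and the Index has not moved.

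**Difference between arms with the same ability path.**

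Control change − intervention change = A6·(difference in I6) − Apre·(difference in Ipre), each difference taken as control minus intervention.

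Suppose importance is equal at baseline, then falls by d in the intervention arm after education and stays there.

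- Baseline as reference: gap = A6·d
- Post-intervention as reference: gap = (A6 − Apre)·d

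**Numbers.** Ability goes from 3 to 6 in both arms, and control importance is 10 throughout. The control change is 60 − 30 = +30 against either reference.

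| Fall in importance | Change vs baseline | Gap | Change vs post-intervention | Gap |
|---|---|---|---|---|
| 1 (10 to 9) | 54 − 30 = +24 | 6 | 54 − 27 = +27 | 3 |
| 2 (10 to 8) | 48 − 30 = +18 | 12 | 48 − 24 = +24 | 6 |
| 4 (10 to 6) | 36 − 30 = +6 | 24 | 36 − 18 = +18 | 12 |

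Every row has the same true ability gain of 3 points in both arms.

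**Different starting values.** With ability 3 to 8 and importance 9, control gains 72 − 27 = +45. If intervention importance falls to 7 and stays there, the change is 56 − 27 = +29 against baseline or 56 − 21 = +35 against post-intervention. The gaps are 16 and 10.

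**The sign can reverse.** In the first example, let importance fall from 10 to 8 after education and return to 10 by 6 months. Against the post-intervention value the change is 60 − 24 = +36, which is 6 points in favour of the intervention. Against baseline there is no gap.

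**Before surgery.** If education leads a patient to name a less important but easier task, 10 × 3 = 30 can become 6 × 5 = 30. The product then shows no change although the expectation changed.

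**Ability alone.** A6 − Apre = 6 − 3 = +3 in both arms in every row of the table.

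**The case against.** The strongest reply is that any distortion between arms is conditional. The article does not say that the programme lowers importance ratings; the stated aim concerns the type of expectations patients set. Patients nominate the items that matter most to them, so importance is likely to be high in both arms, and education may mainly change which goals are named. This stands. A reader might infer that the arms must differ in importance by design, but the documents do not go that far.

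Nor should the 4-point row be taken as the expected size. It moves a self-chosen goal from 10 to 6, out of the article's own high band. Falls of 1 or 2 points stay within that band and give gaps of 3 to 12.

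It can also be said that details such as whether importance is re-rated at 6 months, and which pre-TKA value is the reference, belong in a fuller document. As omissions they are not criticised here. They do not rescue the stated reading in general. Carrying the post-intervention importance forward removes the second term but leaves the first scaled by it, with gaps of 3, 6 or 12 in the illustration. Only carrying baseline importance forward, with baseline as reference, removes the gap, and the article does not say this is done.

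The two domains are also banded separately as low or high. That shows the ratings are kept apart for description, but the fulfilment outcome is still tied to the Index.

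Two further inferences are not supported. One is that the videos cannot change rated ability before surgery: ability is self-rated for named tasks, so it can move if the tasks or the patient's confidence change. The other is that the T0 and T2 labels in the Stage 2 analysis contradict Table 1. Baseline, intervention and post-intervention assessment map naturally to T0, T1 and T2, so the labels are merely undefined.

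**Conclusion.** The point holds in a limited form. The stated reading of the Index difference as ability is wrong whenever importance shifts, and this follows from the article's own definition without any assumption about the data. That the arms could differ on DQO fulfilment with equal recovery is a real possibility in this trial, not a certainty. It requires importance to differ by arm.

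Under the assumed ratings the gap is 6 Index points per point of importance lost against baseline, or 3 against the post-intervention value. If importance falls and stays lower, fulfilment in the intervention arm is understated; if it rebounds, the direction can reverse.

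The reach is one of three measures of one secondary outcome, plus the supporting comparison of open-ended expectation measures before surgery. HSS-TKR fulfilment, activity satisfaction, the primary outcome and the sample size are untouched. The change is worth making because it corrects a stated interpretation at almost no cost.

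**What to change.** Under Expectation Fulfillment, define DQO fulfilment as the change in the ability rating, averaged over items within a person, on the items listed at one named pre-TKA assessment and re-rated at 6 months. Use the same reference assessment in both arms.

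Leave the average unweighted, or weight it only by baseline importance or by normalised importance (ΣI·A / ΣI, with the same weights at both times). Raw post-intervention importance should not be the weight: in the 4-point example it gives 6 × 3 = 18 against 10 × 3 = 30 and keeps the 12-point gap.

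For the pre-surgery comparison in the Stage 2 analysis, analyse importance separately from ability, and name the time points as baseline and post-intervention. Keep the product Index as a descriptive summary.

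The cost is wording and scoring, since both ratings are already collected. There are two downsides. Results will be less directly comparable with the index in the cited study. Also, ability change alone does not remove differences between arms in which tasks are listed after education. Using the baseline list for both arms avoids that, at the price of measuring recovery on goals set before education rather than on any revised goals.

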#### Expectations

As there is no current gold standard for characterizing patient expectations of TKA outcomes, we will be adopting a mixed methods approach and using both standardized self-report, closed-response surveys and open-ended questions to quantify patient expectations and changes in these expectations over time. To evaluate the change in expectations, all participants will be asked to complete the following questionnaires at study entry and following the intervention.

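### DQO fulfilment is scored as a change in an importance-by-ability product, which measures improvement rather than fulfilment, and the pre-surgery reference is not named

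*Protocol article*

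**What the plan says.** All places are in the protocol article.

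- *Direct Questioning of Objectives Questionnaire*: patients choose their own goals ("Participants will be asked to list at least 1 and up to 5 of their most important expectations of TKA surgical outcomes"). Each goal is rated on 11-point scales for importance and for "the current ability to achieve the task / item". Then "A Direct Questioning of Objectives Questionnaire Index (DQO Index) will be derived from the product of the score for each domain". Ratings of 8 or more are read as high.
- *Expectation Fulfillment*: the index is repeated after surgery, and "differences with values obtained prior to TKA will be indicative of the ability to achieve the task". In the same section, HSS-TKR fulfilment is a 1-to-5 rating of how far each expectation was met, and activity fulfilment is a 1-to-7 satisfaction rating. Nothing is subtracted from either.
- *Secondary Outcomes*: all three sit under one label, the "level of patient expectation fulfillment derived from the HSS-TKR questionnaire, the DQO Index, and activity expectations" at 6 months.
- *Expectations* and Table 1: there are two DQO assessments before surgery, since "all participants will be asked to complete the following questionnaires at study entry and following the intervention". The fulfilment section does not say which one supplies the goals and the values to be subtracted.

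**The concern.** The outcome is named as a level but scored as a gain, and the two answer different questions. A patient can reach a goal fully with a small gain, or fall well short of one with a large gain.

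This matters here because the intervention aims to change which goals patients set. If the goals and starting ratings come from the assessment made after the videos, the subtracted quantity is itself open to the intervention. A between-arm difference in gain then mixes what patients attained with where their chosen goals started.

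Separately, the index is a product. If both ratings are repeated at 6 months, a drop in importance lowers the score even when ability has risen. The difference then need not indicate ability, which is what the protocol says it indicates.

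**Working it through.** The protocol gives no numerical figure for DQO fulfilment, so there is none to reproduce. All ratings below are assumed for illustration, and the 11-point scales are taken as 0 to 10.

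**Score as written.** For one goal with importance I and ability a, the index is I × a. The score is I₆a₆ − I₀a₀. With importance held fixed this is I(a₆ − a₀), with maximum I(10 − a₀).

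**1. Gain against level, importance 9.**

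| Goal | Ability before → 6 months | Gain | Maximum gain |
|---|---|---|---|
| Ambitious, partly reached | 2 → 6 | 9 × 4 = 36 | 9 × 8 = 72 |
| Attainable, fully reached | 7 → 10 | 9 × 3 = 27 | 9 × 3 = 27 |

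The fully reached goal gets the lower score, at its own ceiling.

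**2. Between arms.** With common importance I, write Δ₆ for the education-minus-control difference in 6-month ability and Δ₀ for the same difference in starting ability. The difference in gain is I(Δ₆ − Δ₀). With I = 9:

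| Education | Control | Δ₆ | Δ₀ | Gains (education v control) | Reading |
|---|---|---|---|---|---|
| 5 → 8 | 3 → 7 | 1 | 2 | 27 v 36 | reversed |
| 4 → 8 | 2 → 7 | 1 | 2 | 36 v 45 | reversed |
| 4 → 9 | 2 → 7 | 2 | 2 | 45 v 45 | benefit hidden |
| 2 → 8 | 2 → 7 | 1 | 0 | 54 v 45 | no distortion |
| 4 → 8 | 1 → 3 | 5 | 3 | 36 v 18 | favours education |

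A benefit in attainment (Δ₆ > 0) is reversed when Δ₀ > Δ₆, cancelled when they are equal, understated when Δ₀ lies between 0 and Δ₆, and overstated when Δ₀ is negative. In the first row the education arm reaches 8, high by the protocol's own cut-off, while control at 7 does not.

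**3. Which reference.** Baseline ratings precede the intervention, so randomisation makes Δ₀ zero on average, and gain and level then agree between arms. Post-intervention ratings carry no such guarantee.

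**4. Re-rated importance.** Importance 10 → 6 and ability 5 → 8 gives 6 × 8 − 10 × 5 = 48 − 50 = −2, although ability rose by 3. With importance fixed at 10 the change is 10 × 3 = 30.

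**5. The attained level has its own weakness.** A goal at 8 before and after surgery has level 8 and gain 0. A goal going from 2 to 7 has level 7 and ability gain 5. If surgery adds 4 points in both arms and the education arm merely starts at 5 instead of 3, the levels are 9 v 7 and the gains are equal.

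**The case against.** A reader might infer that the score is biased against the education arm and penalises the programme for working. The documents do not support that, for two reasons. It needs the post-intervention DQO to be the reference, and the protocol does not say so. It also needs educated goals to start at higher current ability, and no section states this. Realism concerns what surgery can deliver, so a realistic goal may be rated very low beforehand. An unrealistic goal may gain little because it is not reached, as in the last row of the table under step 2. Both points stand, and the direction is open.

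It can also be said that the DQO follows a cited study that is not available here, that the protocol calls the difference only indicative, and that the between-arm estimator and any adjustment for starting ability may be in an analysis plan. These points limit what can be said about the analysis. They do not remove the mismatch between the outcome's name and its scoring, because both are stated in the article.

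Finally, attainment is already captured by the HSS-TKR and activity measures, and an attained-level score can reward overly modest goals, which the Background section itself warns against. The first limits the consequence. The second is a real cost of the repair and is why the gain should be kept beside it.

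**Conclusion.** The point holds in a conditional form. Without further assumption, a change in the DQO Index is improvement and not a level of fulfilment, it is capped by the starting rating, and the other two fulfilment measures are scored differently. If importance is re-rated, which is the plain reading of repeating the index, the change need not follow ability.

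The effect on the comparison of arms depends on the unnamed reference. With the post-intervention DQO, a benefit in attainment may be understated or reversed. With the baseline DQO, the goal-choice problem largely goes, but the score says nothing about expectations set after education. The document gives no DQO ratings, so neither the size nor the direction of any distortion can be stated; the worked values show only what the scoring rule permits. The reach is one of three measures within one secondary outcome. The primary outcome is untouched.

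**What to change.** In *Expectation Fulfillment* and *Secondary Outcomes*:

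1. Name the pre-surgery DQO that supplies the goals and weights. It should be the post-intervention one if the question is fulfilment of the expectations held after education.
2. Score fulfilment as the 6-month ability on those goals, averaged within patient with the importance ratings from that DQO as fixed weights: Σ wⱼa₆ⱼ / Σ wⱼ. Dividing by the sum of the weights keeps a patient's generally lower importance ratings from shrinking the score.
3. Report the gain with the same fixed weights, Σ wⱼ(a₆ⱼ − a₀ⱼ) / Σ wⱼ, and label it improvement rather than fulfilment.
4. Show starting ability by arm beside both, and state that the attained level can reward goals already nearly achieved before surgery.

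The cost is wording in the protocol and analysis plan. The importance and ability ratings are already collected. It is best settled before outcome data are analysed.
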